#### Qualitative analysis

Reflexive thematic analysis (43) will proceed through both inductive and deductive coding, with initial codes informed by the study objectives and the Theoretical Domains Framework (46) while remaining open to emergent themes. A codebook will be developed iteratively and refined through team discussion. Inter-coder reliability will be assessed on 25% of transcripts using Cohen kappa (*κ* ≥ 0.70 target). Member checking will be offered to consenting participants who wish to review a summary of findings.

#### Mixed-Methods analysis

Following the joint display framework (37), quantitative activity trajectories and qualitative themes will be presented in an integrated matrix organized by study objective. Specific attention will be given to explanatory connections: whether qualitative accounts of motivation, self-efficacy, or technology acceptance help explain observed quantitative variation in activity trajectories and dashboard engagement patterns. Cases of convergence (quantitative and qualitative findings align), divergence (findings conflict), and expansion (qualitative data elaborate or extend quantitative findings) will be explicitly identified and discussed (36).

## Ethical considerations

This protocol reports research involving human participants, including recruitment, continuous monitoring, and semi-structured interviews. Ethical approval has been obtained from the National Healthcare Group Domain-Specific Review Board (DSRB Reference: 2024-3489). Written informed consent will be obtained from all participants or their legally authorized representative. The thermography-based system captures heat signature data only, without personally identifiable visual information, preserving patient privacy. All data will be pseudonymized and stored on secure, encrypted servers compliant with Singapore's Personal Data Protection Act. Participants may withdraw at any time without affecting their clinical care.

For the qualitative component, separate written consent will be obtained for audio recording. Interview transcripts will be de-identified and stored separately from consent forms. A data safety monitoring plan has been developed, with quarterly independent review of adverse events. The study poses minimal risk to participants, as the intervention provides supplementary information to standard rehabilitation care without modifying clinical treatment protocols.

Exercise detection has been categorized by movement magnitude: expansive exercises (e.g., shoulder flexion, hip abduction) are detected with reasonable accuracy; non-expansive exercises (e.g., core stabilization, heel slides) demonstrate limited detection capability; and small-motion exercises (e.g., fist clenching, ankle dorsiflexion) are not reliably detectable by the thermographic system. Assisted exercises are challenging to classify when the assisting person occludes the patient from the camera. Exercise detection is subject to a high false positive rate, with precision estimated at approximately 70% in current evaluation; this reflects the algorithm's tendency to classify repetitive gross movements (e.g., conversational hand gestures, positional adjustments) as exercise. Recall for true exercise episodes remains acceptable, but the low precision necessitates further model refinement prior to Phase 3 deployment.

The system occasionally misclassifies uncommon lying postures as sitting, an issue being addressed through model refinement with additional training data. Three patients remain in the ward at the time of this report. Phase 2 algorithm validation and dashboard co-design are expected to commence in mid-2026. The System Usability Scale instrument has been integrated into the data collection platform in preparation for Phase 2 usability testing. A dashboard co-design meeting was held in April 2026 with clinicians, nursing staff, and the technology partner (CoNEX Healthcare). Key design decisions reached include: (1) a patient activity timeline with hourly granularity using stacked colour bars distinguishing active and inactive periods; (2) a day/night toggle (06:00–22:00 daytime; 22:00–06:00 nighttime) for rest quality and nursing engagement review; (3) a minimum episode threshold of one minute for sitting-out-of-bed counts to reduce noise from transient postural changes; (4) a toggle differentiating assisted from unassisted bed exits to support nursing risk assessment; and (5) a ward-level overview dashboard displaying color-coded nursing engagement duration per bed to support shift-level resource allocation. Patient-facing reporting via printed daily summaries is planned as an interim implementation strategy pending tablet integration, with Phase 3 RMBD evaluation anticipated from end 2026. Final results are expected by 2027.

## Discussion

### Principal considerations

This protocol describes a rigorous mixed-methods approach to evaluating a novel thermography-based AI monitoring and feedback system in inpatient rehabilitation. The randomized multiple baseline design across participants represents a significant methodological advance over the pre-post and simple interrupted time series designs that predominate in digital health evaluations in rehabilitation settings.

The RMBD is well-suited to this study context for several reasons. First, the continuous within-patient time-series data generated by thermographic monitoring creates an unusually rich dataset that is best exploited by designs that model individual trajectories rather than group means at discrete timepoints. Second, the randomization of dashboard onset timing across participants provides a credible basis for causal inference: if activity increases systematically coincide with dashboard activation at five different randomly assigned timepoints, the effect is unlikely attributable to maturation, history, or regression to the mean (27, 28). Third, the design is ethical, as all patients receive the intervention during their admission; the only variation is the timing of onset. Fourth, the design does not require a separate no-treatment control group or multiple wards, making it feasible within a single-site context.

The piecewise multilevel growth model further strengthens the analysis by simultaneously modelling the natural recovery trajectory (pre-intervention slope), the immediate effect of dashboard activation (level change), and the sustained effect (post-intervention slope change), while accounting for between-patient heterogeneity and within-patient autocorrelation (42, 45). This provides more nuanced inference than a simple pre-post comparison.

### Comparison with prior work

To our knowledge, this is the first study to employ thermography-based continuous monitoring with AI-driven activity recognition combined with a patient-facing feedback dashboard in inpatient rehabilitation. Prior studies using wearable accelerometers (10–13) have characterized rehabilitation activity levels but have not closed the feedback loop with real-time patient-facing data. The RMBD also represents a novel application of SCED principles to digital health technology evaluation, extending the design tradition from its origins in behavioural and rehabilitation intervention research (27, 30, 33) to health informatics. Although the multiple baseline design is well-established in SCED methodology, its application with moderately sized samples (*n* = 50) analysed through multilevel modelling represents an innovative scaling of this approach that bridges traditional SCED methodology with group-level inference (42).

The mixed-methods design is aligned with the Medical Research Council framework for evaluating complex interventions (35), which emphasizes understanding not only whether an intervention works but also how and why, and what contextual factors shape implementation. The qualitative process evaluation will generate the mechanistic and contextual insights essential for refining the intervention and planning scale-up.

### Limitations

Several anticipated limitations should be acknowledged. First, the thermographic camera has a limited field of view covering only the bedside area, patient activities outside this zone (therapy gymnasium, bathroom visits, corridor ambulation) are not captured, potentially underestimating total daily activity. A check-in/check-out mechanism will partially mitigate this gap. Second, the single-site design may limit external generalizability, although the ICH serves a patient population typical of tertiary rehabilitation facilities in Singapore, and the qualitative component will explore transferability considerations. Third, the RMBD, while providing strong within-patient causal inference, relies on the assumption that the natural recovery trajectory is adequately modelled by the pre-intervention data points; patients with very short baseline periods (3 days) may have less stable baseline estimates (27, 41). Phase 1 data show substantial length of stay variability (SD 17.0, range 4–70 days), with 18.2% of patients staying fewer than 14 days; patients with short stays assigned to later onset strata will contribute limited post-onset data, though multilevel modelling accommodates unbalanced observations (27, 41). The inclusion of five onset strata and the multilevel modelling approach partially address this concern. Fourth, patients and staff cannot be blinded to dashboard activation, potentially introducing performance or Hawthorne effects; however, the objective, automated nature of the primary outcome measure minimizes this risk. Fifth, the system cannot detect small-motion exercises, and person identification within the camera's field of view remains a technical challenge when visitors or staff are present, although filtering algorithms are in development. Sixth, while the study substantially exceeds minimum SCED standards with 50 participants and five onset strata, the non-concurrent enrolment of participants (patients are recruited as they are admitted) means that the design functions as a non-concurrent MBD, which has been noted to have somewhat weaker internal validity than a fully concurrent design (31, 32); however, the sample size of 50 participants and randomization of onset timing substantially mitigate this concern. Seventh, the DREAMT intervention is multi-component, comprising continuous monitoring, a patient-facing dashboard, therapist-guided goal setting, and a clinician-facing dashboard. Because these elements are introduced together at dashboard activation, the design cannot isolate the independent contribution of any single component, and observed effects should be interpreted as those of the integrated intervention package; the qualitative process evaluation and the planned dose–response analyses of dashboard interaction will be used to generate, but not confirm, hypotheses about which components drive change. Finally, several stated advantages of the design and technology are anticipated rather than demonstrated, and the comparative and causal claims advanced in this protocol will require empirical confirmation once the study is complete.

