### Objectives

The primary objective is to evaluate the effectiveness of the DREAMT intervention (PreSAGE thermography-based AI monitoring with activity feedback dashboard) in increasing daily patient physical activity levels during inpatient rehabilitation, using a randomized multiple baseline design across participants.

The secondary objectives are to: (1) assess the impact on clinical rehabilitation outcomes, including Functional Independence Measure (FIM) scores, Functional Ambulation Category (FAC) scores, Modified Barthel Index (MBI), length of stay, discharge destination, and complications; (2) evaluate the effect on nursing workload distribution and time allocation; (3) explore the experiences, perceptions, and recommendations of patients, nursing staff, and therapists through semi-structured interviews; and (4) integrate quantitative and qualitative findings to develop a comprehensive understanding of intervention effectiveness and implementation considerations.

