### Phase 3: randomized multiple baseline evaluation (months 13–24)

#### Study design

The primary quantitative evaluation employs a randomized multiple baseline design across participants (28, 29, 32), in which each patient undergoes two phases during their admission:
**Phase A (Baseline Observation):** From admission, the PreSAGE system continuously monitors patient activity. Activity data are collected and processed but no feedback is provided to the patient or treating team. This observation-only period provides individualized baseline data for each patient, lasting 3 to 7 days depending on the randomly assigned onset point (see Randomization below), consistent with the A phase in SCED methodology (27, 31).**Phase B (Dashboard Intervention):** At the randomly assigned onset point, the patient-facing dashboard is activated on a bedside tablet and the clinician-facing dashboard becomes available to the treating team. Therapists set personalized activity goals, and patients receive continuous feedback on their progress. Thermographic monitoring continues throughout.The critical design feature is the randomized timing of the A-to-B transition. Each patient will be randomly assigned, using a computer-generated allocation sequence with concealed envelopes, to one of five onset points: post-admission day 3, 4, 5, 6, or 7. If the assigned onset day falls on a weekend, activation will be deferred to the next weekday to ensure research assistant availability and clinical team presence for goal-setting. This ensures that each patient has a minimum baseline observation period of 72 h (to establish a stable pre-intervention trend) while staggering the transition point across the sample in a manner consistent with the MBD framework (29, 32). Ten patients will be assigned to each of the five onset strata, yielding 50 patients total.

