### The DREAMT intervention

The DREAMT intervention is a multi-component digital health intervention comprising:
(1)*Continuous thermographic monitoring:* The PreSAGE system provides automated 24-hour activity data capture, processing, and classification using validated AI algorithms.(2)*Patient-facing feedback dashboard:* For functionally independent patients, the dashboard is accessible via a bedside tablet, displaying daily activity summaries (active time, sitting episodes, exercise counts), graphical progress toward personalized goals, and motivational prompts. For functionally dependent patients who may be unable to independently access the tablet, the dashboard functions primarily as a clinician-facing tool, with the care team using activity data to guide nursing engagement, turning schedules, and early mobilization decisions.(3)*Therapist-guided goal setting:* At the point of dashboard activation, therapists set initial personalized activity goals (e.g., daily minutes of sitting out of bed, exercise repetitions) based on the patient's baseline data and clinical status. Goals are reviewed and adjusted every 2–3 days using dashboard data.(4)*Clinician-facing dashboard:* Providing the care team with activity trend data, nursing engagement metrics, sleep indicators, and patient progress visualizations to support clinical decision-making and care coordination.

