
## Conclusions

The DREAMT study represents a comprehensive evaluation of a privacy-preserving, AI-powered activity monitoring and feedback technology for inpatient rehabilitation. The randomized multiple baseline design across participants exploits continuous within-patient monitoring data to provide causal inference that is stronger than conventional pre-post or interrupted time series designs and more feasible than cluster randomized trials in a single-site context. The embedded qualitative process evaluation will illuminate the mechanisms and contextual factors that shape intervention effectiveness. If the DREAMT intervention proves effective, it could fundamentally transform rehabilitation monitoring from episodic, subjective observation to continuous, objective, personalized, data-driven care thereby optimizing both patient outcomes and nursing resource allocation.

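### The seventh limitation says monitoring starts at dashboard activation, but it runs in both phases; the trial estimates the added effect of dashboards and goal setting under monitoring, not the whole DREAMT package

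*Protocol article*

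**What the plan says.** **Definition of the intervention.** Under Objectives, the primary aim is to "evaluate the effectiveness of the DREAMT intervention (PreSAGE thermography-based AI monitoring with activity feedback dashboard) in increasing daily patient physical activity levels". The section on the DREAMT intervention lists monitoring as component (1): "The PreSAGE system provides automated 24-hour activity data capture, processing, and classification using validated AI algorithms". The other three components are the patient-facing dashboard, therapist-guided goal setting and the clinician-facing dashboard.

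**What changes at onset.** For Phase A, the Phase 3 Study design section says: "From admission, the PreSAGE system continuously monitors patient activity". It adds: "Activity data are collected and processed but no feedback is provided to the patient or treating team". At the assigned day the two dashboards are switched on and therapists set goals. For Phase B it says: "Thermographic monitoring continues throughout". The Figure 1 legend labels the baseline phase as monitoring only.

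**How the result is to be read.** The seventh limitation names all four components, monitoring included, and continues: "Because these elements are introduced together at dashboard activation, the design cannot isolate the independent contribution of any single component". It then says that observed effects belong to the integrated package.

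**What is modelled.** The Quantitative analysis section describes the target as the within-person effect of dashboard activation, with Phase coded 0 at baseline and 1 after activation.

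**What is concluded.** The closing Conclusions section says that, if DREAMT proves effective, "it could fundamentally transform rehabilitation monitoring from episodic, subjective observation to continuous" and data-driven care.

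**The concern.** The limitation is the place where the article tells readers how to interpret the primary result, and its statement about timing is wrong for one of the four components. Monitoring is part of the comparator condition as well as the intervention condition.

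The objective and the intervention definition are therefore wider than the contrast the model estimates. A positive level change would show that dashboards with goal setting add something for patients who are already monitored. Read under the stated rule, it would be reported as the effect of monitoring plus dashboards. It could then be cited in support of moving from manual to continuous AI monitoring.

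The article does not treat monitoring as self-evidently inert. Its rationale for rejecting a parallel-group trial includes an ethical worry about withholding a potentially beneficial monitoring system. The chosen design does not vary that element.

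**Working it through.** The point depends on no figure stated in the plan, so there is none to reproduce. The check sets the sections side by side and then follows the consequence through the model.

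**Step 1. Component by phase** (from the Phase 3 Study design section and the Figure 1 legend)

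| Component | Phase A | Phase B | Differs at onset? | Timing in the seventh limitation |
|---|---|---|---|---|
| Continuous monitoring | on | on | no | starts at activation |
| Patient dashboard | off | on | yes | starts at activation |
| Therapist goal setting | off | on | yes | starts at activation |
| Clinician dashboard | off | on | yes | starts at activation |

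Three rows agree with the limitation. The first does not.

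**Step 2. Consequence in the model.** The fixed part of the primary model is

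E(Y) = γ00 + γ10·Day + γ20·Phase + γ30·Day_post.

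An indicator for monitoring would equal 1 on every patient-day, which is the same column as the intercept. If monitoring shifts activity by a constant m minutes per day, then

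E(Y) = (γ00 + m) + γ10·Day + γ20·Phase + γ30·Day_post.

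Only the intercept absorbs m. γ20 and γ30 do not contain it, and no patient has an unmonitored day from which m could be recovered.

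**Step 3. Numerical confirmation.** One data set was simulated and fitted by generalised least squares.

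- From the Sample size justification section: 50 patients with 10 per onset stratum, 24 days each, residual SD 25 min, between-patient intercept SD 40 min, autocorrelation 0.3, and a level change of 18 min. The baseline of 180 min is implied by that section, since 18 / 0.10 = 180.
- Assumptions of the check: a day slope of 1 min, no slope change, no random slopes, and a constant monitoring effect of m = 20 min. Any constant gives the same pattern.

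| Coefficient | m = 0 | m = 20 |
|---|---|---|
| Intercept (γ00) | 187.6 | 207.6 |
| Day slope (γ10) | 1.43 | 1.43 |
| Level change (γ20) | 15.14 | 15.14 |
| Slope change (γ30) | −0.42 | −0.42 |

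The intercept moves by 207.6 − 187.6 = 20 and nothing else moves. This follows from the algebra. It illustrates which contrast is estimated and is not evidence that monitoring has any effect.

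**The case against.** **The working estimand is already the narrow one.** The analysis section speaks of dashboard activation, the Study design section credits change to the dashboard, and the Figure 1 legend calls baseline monitoring only. The wrong timing appears only in the seventh limitation. This stands, and it means the analysis needs no change. It also shows that the limitation, the objective and the intervention definition are the parts out of line.

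**Monitoring at baseline is intrinsic.** Daily active time is measured by PreSAGE, so an unmonitored phase could not yield the primary outcome. This stands: having monitoring in both phases is disclosed and is not a design flaw.

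**The conclusions are conditional.** They are phrased with if and could, and the Limitations section ends by saying that comparative and causal claims need empirical confirmation once the study is complete. This stands in part. The completed study will not be able to confirm an effect of monitoring itself, because it has no unmonitored comparator.

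**A stronger reading that does not hold.** A reader might infer that nothing in the trial bears on care without AI activity data. The documents do not support that. In Phase A the data reach neither patients nor the treating team, so A versus B does partly compare care without that information against care with it. The Ethical considerations section also describes the intervention as supplementing standard care, so withdrawal of manual observation is not planned. What remains untested is the effect of being monitored and the replacement of manual observation.

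**Conclusion.** The seventh limitation is wrong as written about when monitoring starts and, as a result, about what the effect represents. γ20 and γ30 estimate the added effect of the patient dashboard, clinician dashboard and therapist goal setting under continuous monitoring. The limitation is right that those three cannot be separated from one another.

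One of four named components has zero contrast between phases, so its constant effect is unidentified whatever the sample size. A reader might want to convert this into a bias in minutes per day. The documents give no figure for an effect of silent monitoring, so no such number is supportable. If silent monitoring does nothing, the numerical consequence is nil and only the wording is at fault, but the article does not state that assumption.

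Exact cancellation rests on the monitoring effect being constant over the stay. Reactivity that fades over the first days need not drop out cleanly.

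The trial remains valid for the narrower question. Because the correction changes what may be concluded, it is more than clerical.

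**What to change.** 1. **Limitations, seventh point.** Say that monitoring is common to both phases. Say that only the two dashboards and goal setting start at activation, and that these three cannot be separated from one another. Replace the reference to the integrated package accordingly.
2. **Objectives and the DREAMT intervention section.** Align both with the contrast in the Quantitative analysis section, for example: *the effect on daily active time of adding the patient dashboard, clinician dashboard and therapist goal setting to continuous thermographic monitoring*. Monitoring can then be described as the platform and measuring instrument present throughout.
3. **Conclusions, in the Abstract and at the end.** Limit them to the feedback and goal-setting package. Note that the effect of monitoring itself and the replacement of manual nursing observation are not tested.

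The cost is a few sentences and a narrower claim. No change to design, randomization, sample size, model or data collection follows. The Results section places Phase 3 from the end of 2026, so the wording can be settled before the evaluation begins.
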